**Methods:**

The objective of this project is to validate a dosimetry model based on the relationship between the effects of photobiomodulation with anthropometric and hemodynamic variables, both in local application and systemic application in patients with symptoms of orofacial pain and tension headache. For this purpose, 180 participants with orofacial pain post-covid eligible participants will be randomly assigned to Group 1—Local Photobiomodulation, Group 2—Vascular Photobiomodulation, Group 3—Placebo Local Photobiomodulation, or Group 4—Placebo Vascular Photobiomodulation [Therapy EC–DMC device, São Carlos, Brazil,– 660 nm, 100mW] using stratified block randomization. Before the application, sociodemographic information such as age, skin phototype [classified by the Fitzpatrick scale], weight, height, body mass index [BMI], oxygen saturation [SaO2], blood pressure [BP], heart rate [HR], and thickness of skin, fat, and facial muscles will be collected. During the application, we will collect local temperature, SaO2, BP, and HR. Before and after laser application, blood levels of lactate and hemoglobin, BP, and HR will be measured in the first and last session. In addition to demographic, anthropometric, and hemodynamic variables, the penetrated energy will be quantified using a power meter, and information from orofacial pain and headache symptom questionnaires will be analyzed. The Monte Carlo simulation technique will be used to systematically study the relationship between the light penetration profile into the target tissues and the most relevant variables, namely BMI, tissue layer thicknesses, and skin phototype. Light transmittance, measured in vivo and simulated, will be compared to validate a personalized dosimetry model.

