#### Thickness of the fat and muscle layer of the face

The BodyMetrix 2000 device, a linear ultrasound with a depth of 60mm, will be used to assess the thickness of the facial muscles. The method is safe, emits no radiation, and is non-invasive. During the assessment, the participant will remain in a comfortable position, and a conducting gel will be applied to the skin over the masseter. The device will be slid from the origin to the insertion of the muscle, aiming to obtain precise information. The ultrasonographic images generated will be subsequently analyzed using the BodyView software, for thickness of tissue layers in the facial region.

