#### Monte Carlo simulation

The Monte Carlo technique will be employed to simulate the fluence profile, energy deposited in different tissue layers of the cheek and index finger, and transmittance, using light of wavelengths 660 nm and 808 nm. In an initial phase, a Monte Carlo model will be developed, considering the morphological structure of the tissues to be treated, approximating their structure to a planar and laminar model consisting of four layers: epidermis, dermis, subcutaneous fat, and muscle [15].

The thicknesses of each layer will be obtained from the literature, and their values will be varied in predefined intervals consistent with literature findings for different age groups and BMI values. The optical properties of each layer, including absorption and scattering coefficients, anisotropy coefficient, and refractive index, will be gathered from bibliographic research, considering the expected variability for the sample under study.

A model for the absorption coefficient will be used, accounting for blood content in each layer, blood oxygen saturation level, as well as fractions of fat, melanin, and water in each tissue layer. Based on the preliminary study, a database will be established aiming to establish a relationship between energy deposited in tissues and different anthropometric characteristics [13, 16].

Special attention will be given to the relationship between energy deposited in the epidermis and muscle, to establish a compromise between safety limits and treatment effectiveness. Simulated transmittance values will be subsequently compared with values measured in volunteers, considering measurements of tissue thickness by ultrasound, skin type, BMI, and blood saturation levels. A computational implementation of the tissue optical model and the Monte Carlo simulation model will be developed based on Marti et al.’s MCMatlab code, available online [https://github.com/ankrh/MCmatlab], using Matlab® software, version 2022.

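### The energy database rests on literature thicknesses by age and BMI, the cheek validation considers ultrasound thickness, and no stated comparison isolates the age/BMI-to-thickness step

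*Protocol article*

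**What the plan says.** The Monte Carlo simulation section describes two stages.

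- **Building.** In an initial phase the tissue is modelled as four flat layers (epidermis, dermis, subcutaneous fat, muscle). "The thicknesses of each layer will be obtained from the literature, and their values will be varied in predefined intervals consistent with literature findings"; the intervals differ by age group and BMI. Then: "Based on the preliminary study, a database will be established aiming to establish a relationship between energy deposited in tissues and different anthropometric characteristics".
- **Comparing.** "Simulated transmittance values will be subsequently compared with values measured in volunteers". The article adds that this second stage is carried out "considering measurements of tissue thickness by ultrasound, skin type, BMI, and blood saturation levels".

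The abstract (Methods) gives the purpose of the second stage: "Light transmittance, measured in vivo and simulated, will be compared to validate a personalized dosimetry model". It describes the inputs of interest as "the most relevant variables, namely BMI, tissue layer thicknesses, and skin phototype", and lists BMI among the baseline data together with the statement that "thickness of skin, fat, and facial muscles will be collected".

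The section on the thickness of the fat and muscle layer of the face describes an ultrasound device that "will be used to assess the thickness of the facial muscles", applied over the masseter. The Light transmission section has transmission measured at two sites, the cheek and the index finger.

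**The concern.** The stated objective is a dosimetry model based on anthropometric and hemodynamic variables. The Introduction gives as its rationale that layer thickness varies with body composition. A chain from anthropometry to light has two links: age and BMI to layer thickness, then layer thickness to light. The database contains both links, and the first comes from the literature. If the cheek comparison is run with each participant's own ultrasound thickness, it exercises only the second.

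What is at stake is the scope of the conclusion. A close match at the cheek could be reported as validating dosimetry from anthropometry when it had validated light transport given measured thickness. The participants are 7 to 19 years old, an age range over which thickness for a given BMI may well shift, so the first link should not be taken on trust.

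**Working it through.** The plan has no figure to reproduce here, and the sample of 180 is a convenience sample that plays no part in the argument. The check is a comparison of inputs.

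| | Database | Cheek comparison |
|---|---|---|
| Source of thickness | literature intervals by age group and BMI | participants' ultrasound is considered |
| Role of BMI | indexes the thickness intervals | listed beside measured thickness |
| Output | deposited energy by layer | transmittance |
| Checked against | nothing stated | power-meter reading |

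1. In the model as described, light depends on layer thickness and on optical properties. Absorption is built from blood content, oxygen saturation, and the fractions of fat, melanin and water. BMI is not itself an optical quantity, so it can act only through thickness or composition.
2. Once measured thickness is supplied, BMI can act only through composition. Its path through thickness is bypassed.
3. Agreement between simulated and measured cheek transmittance then supports the link from thickness to light. It is uninformative about the link from age and BMI to thickness.
4. No sentence compares the literature thicknesses with the ultrasound values, revises the database from them, or commits to a run with age/BMI-based thickness alone.
5. The data for such a check exist at the cheek. Age, weight, height and BMI are recorded, as are skin, fat and muscle thickness. The thickness check needs no laser light, so all four groups can contribute.
6. Deposited energy is not measured in participants. Even a good check reaches it only indirectly, through transmittance.

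**Illustration of size, on assumed values only.** Neither input is in the documents. If thickness is wrong by Δz and effective attenuation is μ, transmittance is wrong by a factor of about exp(μ·Δz):

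- μ = 0.1 per mm, Δz = 1 mm: exp(0.1) = 1.11
- μ = 0.2 per mm, Δz = 2 mm: exp(0.4) = 1.49
- μ = 0.3 per mm, Δz = 3 mm: exp(0.9) = 2.46

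This shows only that the skipped link could matter. It does not estimate by how much in this trial.

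**The case against.** The other side has several good points.

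- **Building on literature values and then validating on measured people is a normal sequence, not a contradiction.** The literature stage can be read as a sweep over plausible thicknesses, with each volunteer later placed within it. The text says ultrasound is considered; it does not say that ultrasound replaces the literature values. This stands. Even on that reading, though, placing a person by ultrasound does not test placing that person by age and BMI.
- **BMI is among the comparison variables.** This is true, and how it enters (as input, stratum or regressor) may be set out in a full protocol or analysis plan that is not shown. A reader might infer that the BMI-to-energy step is never tested. The documents do not support that; they show only that no stated comparison isolates it.
- **The final model may require ultrasound.** The abstract names layer thickness and phototype as well as BMI. A reader might infer that BMI-to-energy is the step that personalises the dose, and that clinicians would work from BMI, age and phototype alone. The text describes no such user. What remains is conditional: any use of the database from anthropometry alone depends on the unchecked link.
- **The index finger has no described ultrasound.** Simulations there must take thickness from elsewhere, so that comparison does expose non-ultrasound inputs to measurement. It says nothing, however, about how cheek thickness varies with age and BMI.

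**Conclusion.** The point holds in a limited form. The database is tied to literature thicknesses indexed by age group and BMI, while the cheek comparison is described as considering each participant's ultrasound thickness. As described, good agreement would validate light transport given measured thickness, not the database. This rests on the natural reading that ultrasound values enter the cheek simulations, and it applies to the cheek only.

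The size cannot be derived from the documents. The factor of about 1.1 to 2.5 is an illustration on assumed inputs and should not be cited as a finding. Nothing here invalidates the trial or its simulation work. What is affected is how far the word validated can reach, and that is worth settling before the comparison is run.

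**What to change.** Amend the Monte Carlo simulation section, for the cheek:

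1. Compare the literature thickness values by age and BMI with participants' ultrasound thickness of the same layers. Revise the database intervals where they disagree. The model separates epidermis and dermis while the abstract lists skin thickness as one item, so state how skin will be matched.
2. Run the cheek transmittance comparison with ultrasound thickness, and again with thickness from age and BMI alone. Do the second run with the literature values and with values predicted from the trial's own data. Make those predictions out of sample, for example by cross-validation, so that the same participants do not both fit and test them. Report the error with ultrasound thickness and the error with age/BMI-based thickness side by side.
3. Limit the validation claim to the inputs tested. Claim dosimetry from age and BMI without ultrasound only if the second error is acceptable, judged by a criterion set beforehand. State that deposited energy is checked only indirectly, through transmittance.

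The cost is some extra analysis and simulation time, with no new measurements. The likely downside is a larger reported error for the age/BMI-based model.

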### Study variables

Sociodemographic information such as age, skin phototype [classified by the Fitzpatrick scale], weight and height. The primary outcome is orofacial pain, and the secondary outcomes are oxygen saturation, blood pressure, heart rate, local temperature, blood lactate levels, and hemoglobin levels. In addition to demographic, anthropometric, and hemodynamic variables, the penetrated energy will be quantified using a power meter, and information from orofacial pain and headache symptom questionnaires will be analyzed.

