#### Light transmission

The SPER Scientific Pocket Laser Power Meter device [Scottsdale, AZ, USA] will be used. Light transmission will be assessed through the index finger and cheek [masseter] of each participant. The sensor of the equipment will be positioned on the inner region of the cheek at the same time the researcher is applying the laser on the masseter region [2 points].

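### Agreement on transmittance is named as the validation of the dosimetry model, but it does not by itself confirm the epidermis and muscle energies the model is used for

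*Protocol article*

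**What the plan says.** The abstract's Methods paragraph names the validation step: "Light transmittance, measured in vivo and simulated, will be compared to validate a personalized dosimetry model". The Monte Carlo simulation section repeats it and adds the participant-level inputs: "Simulated transmittance values will be subsequently compared with values measured in volunteers, considering measurements of tissue thickness by ultrasound, skin type, BMI, and blood saturation" level. No other in vivo comparison is named.

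The Light transmission section describes the measurement: "Light transmission will be assessed through the index finger and cheek [masseter] of each participant". For the cheek, "The sensor of the equipment will be positioned on the inner region of the cheek", that is, beyond all the tissue between laser and mouth.

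The same Monte Carlo section gives the model a different working output. It plans a database "aiming to establish a relationship between energy deposited in tissues and different anthropometric characteristics", and then states: "Special attention will be given to the relationship between energy deposited in the epidermis and muscle", so as to balance safety against effect. The model has four layers (epidermis, dermis, subcutaneous fat, muscle). Their absorption, scattering, anisotropy and refractive index are taken from published sources, allowing for expected variability. The abstract's Discussion paragraph says that the results help validate a model for calculating appropriate dosimetry.

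**The concern.** The quantity tested and the quantity used are not the same. The meter records light that no layer absorbed and that left on the far side. The safety and effectiveness comparison needs the light absorbed in two particular layers. Different combinations of layer absorption and scattering can give one exit value with different depositions.

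If measured and simulated transmittance agree, the stated rule leads to a claim that the dosimetry model is validated. The epidermal figure (the safety side) and the muscle figure (the target side) would share that label without having been tested. Validating this model is the study's declared aim, so the point bears on its main conclusion.

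**Working it through.** The article gives no optical coefficients, so there is no figure of its own to reproduce. The check asks how far layer deposition can move while transmittance stays exactly the same.

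**Inputs, all assumed except the layer count and the 6 J per point.** Thicknesses: epidermis 0.1 mm, dermis 1.5 mm, fat 3 mm, muscle 10 mm. Reduced scattering: 30, 18, 11 and 8 per cm. Absorption: dermis 0.4, fat 0.2 per cm; reference values epidermis 5, muscle 0.40 per cm.

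**Method.** One-dimensional diffusion through four layers: −d/dz(D·dφ/dz) + μa·φ = S, with D = 1/[3(μa + μs′)]. S is the light scattered out of a collimated beam that decays at rate μa + μs′. The outward flux at each face is φ/(2A), with A = 2.5. Deposition in a layer is the integral of μa·φ plus the directly absorbed part of the beam. Transmittance, reflectance and the four depositions sum to 1 in the runs checked.

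**Step 1: vary epidermal absorption and re-solve muscle absorption for identical transmittance (0.5705%).**

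| Epidermis μa (per cm) | Muscle μa (per cm) | Epidermis | Muscle | Ratio |
|---|---|---|---|---|
| 3.5 | 0.409 | 12.2% | 11.0% | 1.11 |
| 4 | 0.406 | 13.8% | 10.8% | 1.27 |
| 5 | 0.400 | 16.7% | 10.5% | 1.58 |
| 6 | 0.394 | 19.4% | 10.3% | 1.89 |
| 7 | 0.389 | 22.0% | 10.0% | 2.21 |

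From the first row to the last, muscle absorption moves by (0.409 − 0.389)/0.400 = 5%. At 6 J per point, epidermal energy goes from 0.122 × 6 = 0.73 J to 0.220 × 6 = 1.32 J. Muscle energy goes only from 0.66 J to 0.60 J.

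**Step 2: hold the epidermis at 5 per cm and trade muscle scattering against muscle absorption at the same transmittance.** Reduced scattering of 5 per cm with absorption 0.589 gives muscle deposition of 12.2%. Scattering of 12 with absorption 0.267 gives 8.8%.

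**Step 3: sensitivity.** With A between 2.0 and 2.95, the 3.5 to 7 per cm span gives epidermal deposition of 11.1–20.3% to 13.1–23.4%, and ratios of 1.08–2.15 to 1.13–2.25. In another assumed geometry (fat 4 mm, muscle 8 mm, reduced scattering 20, 15, 10 and 6 per cm, transmittance fixed at 1.85%), doubling epidermal absorption from 3 to 6 per cm moves the epidermis from 10.7% to 19.5% and the muscle from 12.8% to 11.7%. The ratio doubles there too, from 0.84 to 1.67.

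**The case against.** **Much of what drives deposition is recorded.** Phototype, ultrasound thickness, BMI and saturation enter the comparison. A reader who sets light against dark epidermis could infer a far larger ambiguity: a photon Monte Carlo run with the same fat, muscle and scattering values, and epidermal absorption from 1 to 25 per cm, gives epidermal deposition of 4.8% to 54.1% (11-fold) at transmittances of 0.64% to 0.69%. The documents do not support that as uncertainty within one participant, since those values describe different skin types. With epidermal absorption known to within 20% (4 to 6 per cm), the range is about 14% to 19%. What remains is that phototype is an ordinal class and not an absorption coefficient.

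**The comparison is informative.** It spans two sites and participants of varied phototype and thickness. With muscle absorption fixed at 0.40 per cm, moving the epidermis from 1 to 25 per cm changes transmittance from 0.63% to 0.39% (1.6-fold), so a grossly wrong epidermal model could be exposed. That stands. Over 3.5 to 7 per cm, however, transmittance moves only from 0.592% to 0.545%, about 8%, while epidermal deposition nearly doubles.

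**The plan predicts forward and states no fitting to the reading.** True, but a correct prediction of a total still does not show that its components are correct.

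**No dose in this trial depends on the model.** A reader might infer that participants would be dosed from untested energies. The Interventions section and Table 1 fix the trial's parameters in advance, and the abstract says only that the results contribute to validation. The issue is the claim drawn afterwards.

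**An article condenses.** How input variability is carried through may be set out elsewhere. The validation criterion itself is stated here twice, so the point does not rest on an omission. Describing the reading as penetrated energy in Study variables is only a matter of wording, since other sections call it light transmission.

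**Conclusion.** The point holds in a limited form and should be addressed. The stated comparison tests predicted transmittance at the finger and cheek. It can count against the model, but it cannot alone confirm energy deposited in epidermis or muscle.

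Under the assumed cheek, one transmittance is compatible with epidermal deposition of about 14–19% for a narrow spread of epidermal absorption and 12–22% for a twofold spread, with an epidermis-to-muscle ratio of 1.1 to 2.2. Muscle deposition ranges over about 9–12% when its scattering and absorption are traded. These sizes depend on the assumed coefficients and on how tightly phototype limits epidermal absorption, which the article does not say. The non-uniqueness itself does not depend on those values.

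**What to change.** In the abstract's Methods paragraph and the Monte Carlo simulation section, state that the comparison validates predicted transmittance at the measured sites, and that simulated epidermis and muscle energies are model-based and not directly validated.

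Report those energies as a range. Given each participant's phototype, thickness, BMI and saturation, retain the literature-plausible optical properties whose simulated transmittance is consistent with the measured value within measurement error, and give the spread of deposition over them. Carry that spread, and not a single value, into the comparison of safety with effectiveness.

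The cost is extra simulation runs, a stated measurement error for the power meter, and a narrower and less precise claim about layer energies. No new participant data are needed.

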#### Hemoglobin level

The hemoglobin level will be analyzed before treatment, immediately after the first session, and after the last session. The same puncture performed for lactate collection will be used for hemoglobin analysis. The blood drop will be analyzed by the Hb Analyzer ECO CARE [Eco Diagnóstica, Nova Lima, MG, Brazil].

The variables of heart rate, blood pressure, oxygen saturation, light transmission, and local temperature will be collected during the application of photobiomodulation, which will take place in a private setting in the dental office of the Health Sector Nucleus of the Teaching Center. The Handheld–Vital Sign Monitor will be used for collecting these variables.

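### Measured hemoglobin is not among the named individual inputs to the comparison of simulated with measured transmittance, so some avoidable person-to-person error may remain in the validation

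*Protocol article*

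**What the plan says.** The Monte Carlo simulation section builds an absorption coefficient "accounting for blood content in each layer, blood oxygen saturation level, as well as fractions of fat, melanin, and water in each tissue layer". Optical properties come from the literature: they "will be gathered from bibliographic research, considering the expected variability for the sample under study". Simulated transmittance is then compared with transmittance measured in volunteers, "considering measurements of tissue thickness by ultrasound, skin type, BMI, and blood saturation levels". These four are the only individual measurements named for that step.

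The Hemoglobin level section states: "The hemoglobin level will be analyzed before treatment, immediately after the first session, and after the last session". The Study variables section gives hemoglobin the role of an outcome: "the secondary outcomes are oxygen saturation, blood pressure, heart rate, local temperature, blood lactate levels, and hemoglobin levels". No section connects it to the simulation.

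The abstract's Methods paragraph states the objective as to "validate a dosimetry model based on the relationship between the effects of photobiomodulation with anthropometric and hemodynamic variables", and the Introduction's hypothesis likewise pairs the two kinds of variable. The same Methods paragraph describes the simulation as studying light penetration against "the most relevant variables, namely BMI, tissue layer thicknesses, and skin phototype".

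**The concern.** The validation asks how well a model with individual inputs predicts each participant's transmittance. Any true difference between participants that affects transmittance but does not enter the model shows up as disagreement between simulated and measured values.

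Hemoglobin is a candidate for such a difference. At a given blood fraction and saturation, absorption by blood is proportional to hemoglobin concentration, while saturation sets only the split between its oxygenated and deoxygenated forms. The list includes saturation and omits the other measured blood quantity. If the simulations follow the list as written, part of the disagreement could have been removed with data already in hand, and an available test of one hemodynamic variable would not be made. Because this error belongs to the individual participant, a larger sample does not remove it from individual predictions.

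**Working it through.** The protocol states no blood fraction, hemoglobin range, absorption coefficient or agreement limit, so there is no figure to reproduce. The calculations below are illustrations on assumed inputs.

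**Assumed inputs (none is in the document).** Hemoglobin 11 to 16 g/dL at ages 7 to 19, reference 13.5 g/dL; reduced scattering s = 8/cm; non-blood absorption 0.1/cm; blood absorption b = 0.05 to 0.2/cm at the reference; tissue thickness d = 1.0 to 1.5 cm.

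**Formulas (diffusion approximation).** Absorption a = 0.1 + b × Hb/13.5. Effective attenuation m = √(3a(a + s)). Transmittance is proportional to exp(−m d), so the ratio between two hemoglobin values is exp(d × difference in m).

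**Step 1: the two extremes, 11 against 16 g/dL.** The blood term is multiplied by 11/13.5 = 0.815 and 16/13.5 = 1.185.
- b = 0.05/cm, d = 1.0 cm: m = 1.854 and 1.974; ratio exp(1.0 × 0.120) = 1.13.
- b = 0.2/cm, d = 1.5 cm: m = 2.553 and 2.903; ratio exp(1.5 × 0.350) = 1.69.

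Against a model set at 13.5 g/dL, a participant at either end differs by about 6% in the first case and by −23% to +31% in the second.

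**Step 2: a more typical deviation.** If 11 to 16 g/dL spans about four standard deviations, one is 5/4 = 1.25 g/dL, or 9.3% of the reference.
- b = 0.05/cm, d = 1.0 cm: m moves from 1.915 to 1.945 or 1.885, and transmittance changes by about 3%.
- b = 0.2/cm, d = 1.5 cm: m moves from 2.733 to 2.819 or 2.645, and transmittance changes by −12% or +14%.

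**Step 3: comparison with other sources of variation, same formula.**
- A 1 mm smaller thickness raises transmittance by exp(0.1 × 1.915) − 1 = 21% to exp(0.1 × 2.733) − 1 = 31%. Thickness is already an individual input.
- Moving b from 0.05 to 0.2/cm, as an uncertain layer blood fraction might, changes transmittance by exp(1.0 × 0.818) = 2.3-fold at 1.0 cm and 3.4-fold at 1.5 cm.

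**Step 4: a second parameterisation.** Let T = exp(−D), with D proportional to the square root of absorption and a share f of absorption due to blood. The relative error is exp(−D(√(1 + f × dev) − 1)) − 1, where dev is the relative deviation of the blood term.

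| Assumed case | Hb off by 10% | Hb off by 20% | Layer blood fraction off by 50% |
|---|---|---|---|
| D = 2, f = 0.1 | about 1% | about 2% | about 5% |
| D = 4, f = 0.4 | about 8% | 15% to 18% | 32% to 53% |
| D = 6, f = 0.8 | 21% to 28% | 37% to 65% | 67% to 287% |

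Both calculations show an effect that runs from negligible to large depending on inputs the protocol does not give, and a blood-fraction error that can exceed the hemoglobin error.

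**The case against.** The strongest reply is that silence is not exclusion. The list is not said to be complete, no section says hemoglobin will be held at a literature value, and a condensed article may leave the parameterisation to a fuller document. This stands: a reader might infer that hemoglobin has been ruled out, and the text does not say so. What remains is that the article is specific at this step, naming four inputs with one blood variable among them and leaving out the other that is measured.

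Three further inferences are tempting, and the document does not support them.
- That blood content dominates the absorption model. It is one of several terms listed, and the abstract names BMI, layer thickness and phototype as most relevant.
- That the hemodynamic part of the model goes untested. Saturation is named as an individual input. That it varies too little between outpatients to matter is stated nowhere.
- That using hemoglobin would remove the blood-related error. A finger-prick value is a concentration in blood, whereas the model also needs the blood fraction of each layer, which is not measured. Only part of the error is avoidable.

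It is also fair to say that the 1.13- to 1.69-fold range contrasts extremes, and that nothing is lost irreversibly, since the values are collected and can be added later.

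**Conclusion.** The point holds as a limited one about model inputs. No stated figure is wrong and no two passages conflict. A quantity that is measured before treatment and that scales blood absorption is not named as an input to the validation, although the aim includes hemodynamic variables. Some avoidable person-to-person error may therefore remain.

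Its size cannot be derived from the document. On the assumed optical properties it is about 3% to 14% in transmittance for an assumed 1.25 g/dL deviation; the upper illustration is 1.13- to 1.69-fold between 11 and 16 g/dL. For a typical participant this is less than the effect of 1 mm of tissue on the same assumptions, and the unmeasured layer blood fraction remains whatever is done with hemoglobin. The improvement is worth making because it costs almost nothing and tests part of the stated hypothesis.

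**What to change.** In the Monte Carlo simulation section, add pre-treatment hemoglobin to the individual inputs: multiply the literature blood absorption term of each layer by measured/reference hemoglobin, and state the reference value. Report agreement between simulated and measured transmittance with and without this scaling. Add a sensitivity run over a plausible range of the assumed layer blood fraction, so that the gain from hemoglobin can be judged against the blood-related error that remains. If hemoglobin is deliberately left out, say so and give the reason.

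The cost is one scaling factor in the code and extra simulation runs. No new data collection, visits or participant burden are needed.
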